## 3. Materials and Methods

The diagnostic accuracy study will be conducted at the Department of Otorhinolaryngology, Head and Neck Surgery, and Audiology, University Hospital of Copenhagen, Rigshospitalet (RH), Copenhagen, Denmark. The protocol adheres to recommendations for interventional trials described in the SPIRIT and STARD guidelines [47]. 

Patients diagnosed with tongue SCC will be invited to participate in the study. All participants meeting the inclusion criteria (described in Section 3.1) will undergo a preoperative in vivo ultrasound scan to measure the depth of invasion. Perioperative ex vivo 3D ultrasonography of the resected tongue tumor will then be performed. Furthermore, the surgeon will assess the surgical margins by clinical examination of the resected specimen ex vivo. Then, the surgical specimen will be MRI scanned at Department of Radiology immediately after surgery. Afterwards, the surgical specimen will be transferred to the pathology department for a formalin fixation procedure. On the day after the surgery, the surgical specimen will also be scanned by 3D ultrasound after formalin fixation. Surgical margin assessment results from the surgeon assessment, MRI, and the 3D ultrasound scan of the surgical specimen will be correlated to the final histopathology report. 

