## 4. Clinical Outcome Definition

We will compare the surgical margin assessment in tongue cancer specimens by comparing three index tests (clinical examination, 3D ultrasound, and MRI) with the post-surgical histopathology assessments as the reference standard. 

The primary outcome will be reported as:The perioperative measurement of resection margins (mm) at five directions (Figure 1) with clinical exam and imaging compared to the post-surgical histopathology results (reference standard).The image-by-image comparison of the depth of invasion measurement (mm) from 3D ultrasound/MR imaging and histopathology slides.The depth of invasion (mm) comparison between in vivo and ex vivo ultrasound.The number of margins correctly classified as free (>5 mm), close (1–5 mm), or positive (<1 mm) margins by 3D ultrasound and MRI using histopathology findings as the reference.

The secondary outcome will be: The number of cases requiring adjuvant treatments (surgery or chemo/radiotherapy) due to T-site residuals.A change in tumor volume and resection margin measurements with 3D ultrasound imaging before and after formalin fixation.The time usage (minutes) and cost estimation for perioperative 3D ultrasound and MRI.

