## 5. Statistics

There will be three index tests used for clinical examination, 3D ultrasound imaging, and MRI of the ex vivo specimen. The reference standard will be the final histopathology result. Each case will undergo five margin measurements (anterior towards the apex of the tongue, posterior towards the base of the tongue, medial, lateral, and profound/deep margins) by three index tests and one standard reference. Tumor and specimen volume will be calculated for each case. The deep margin will be measured at equally distanced planes of imaging in every case, and the results will be correlated to the corresponding deep margin measurements from the reference standard.

The participants will be excluded from the final analysis in case of any technical issues such as non-feasibility to perform parallel slicing of the surgical specimen or patients with MRI contradictions (pacemaker, metal implants not compatible with MRI, etc.). The number of excluded participants will be reported as non-conclusive cases and will be excluded from the study.

Margin measurements (quantitative data in mm) and tumor and specimen volume measurements (quantitative data in ml) will be presented as an averaged value over two measurement repetitions, as described in Section 3.2. The measurement differences between the index tests and the reference standard will be compared by a paired *t*-test. The degree of correlation will be expressed using Pearson’s correlation coefficient, in which the index tests and the reference standard will be considered to be significantly correlated when *p* < 0.05. To evaluate the agreement between the index tests and the reference standard, we will also analyze the data using Bland–Altman plots, which show the mean difference between the two techniques with a 95% confidence interval. This allows for easy interpretation of whether the differences between the index tests and the reference standard are clinically relevant. Correlation between the plane-by-plane deep margin measurements obtained by the reference standard and the index tests will be evaluated by *t*-test, and the threshold for significance correlation will be *p* < 0.05. The correlation between the depth of invasion measurements (mm) from in vivo ultrasound and the ex vivo ultrasound will also be reported.

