## 6. Power Calculation and Inclusion Period

A power calculation was based on the expected change in frequency between the free margin status when diagnosed by ultrasound imaging of the surgical specimen and when evaluated using the conventional procedure in the operation theater, without using ultrasound. The sample size needed to compare two independent binomial proportions is calculated to achieve a significance level of 0.05 and 90% power. The power calculation is based on results from Koning et al. [18] that found the frequency of free margin status to be 55% using ultrasound and 16% in the conventional cohort. A 2-sample paired binary sample size calculation results in the sample size of n = 27. By estimating a 10% drop-out rate, due to technical reasons, we will aim to include 30 cases. 

In Denmark, oral cavity cancer is the second most common head and neck cancer, and it has previously been reported with an incidence of 3.5 pr. 100,000. The uptake for the Rigshospitalet Center averages more than 90 cases annually, with 1/3 being tongue tumor cases [2,49]. In Denmark, all cancer investigations and treatments take place in public hospitals, free of charge, and financed by taxes. Based on the Copenhagen oral cavity squamous cell carcinoma database [6], we expect more than 30 patients annually to be diagnosed with tongue SCC, and these are the potentially eligible participants. Some of these patients will not fulfill the inclusion criteria, and some will decline to participate in the study. Therefore, we expect to include roughly 60% of the patients over a 1.5 year period. All enrolled patients are included in the analysis, with an intention-to-treat assumption [50]. We will register the age, sex, and final pathology staging of all the eligible participants to assess the comparability of the indexed population to the recurrent general tongue cancer population.

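### The primary in vivo versus ex vivo depth-of-invasion comparison has correlation as its only named analysis, and correlation cannot show a systematic shift between the two scans

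*Protocol article*

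**What the plan says.** Section 3 of the protocol article states that all participants "will undergo a preoperative in vivo ultrasound scan to measure the depth of invasion". Section 4 then lists two depth-of-invasion items within the primary outcome:

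- "The image-by-image comparison of the depth of invasion measurement (mm) from 3D ultrasound/MR imaging and histopathology slides"
- "The depth of invasion (mm) comparison between in vivo and ex vivo ultrasound"

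For the second item, Section 5 names one analysis: "The correlation between the depth of invasion measurements (mm) from in vivo ultrasound and the ex vivo ultrasound will also be reported".

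The same section uses stronger methods elsewhere, but fixes their scope. On the paired t-test it says: "The measurement differences between the index tests and the reference standard will be compared by a paired" t-test. On agreement it says: "To evaluate the agreement between the index tests and the reference standard, we will also analyze the data using Bland–Altman plots". It also defines the index tests: "There will be three index tests used for clinical examination, 3D ultrasound imaging, and MRI of the ex vivo specimen". Histopathology is the reference standard.

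**The concern.** Comparing depth in the patient with depth in the resected specimen should answer whether the measurement changes on resection, and by how much. Correlation answers a different question: whether deep tumours on one scan are also deep on the other. It can be high while every ex vivo reading is millimetres away from its in vivo counterpart.

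The absolute value matters by the protocol's own account. The Introduction says that depth of invasion bears on T-classification, and a secondary outcome already looks for dimensional change before and after formalin fixation. If correlation is all that is reported, a reader could take a high coefficient as evidence that the two scans are interchangeable when no estimate of their difference has been given.

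**Working it through.** **1. Which planned methods reach this pair?**

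- Paired t-test and Bland–Altman plots: index test against reference standard. The preoperative in vivo scan is not one of the three index tests, and ex vivo ultrasound is not the reference standard. The pair is outside both methods.
- Intraclass correlation (Section 5): concerns variability within and between observers, not the two scan settings.
- Plane-by-plane analysis (Section 5): concerns the deep margin, not depth of invasion.
- Correlation: the only method named for the pair.

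**2. What can correlation show?** Let x be in vivo depth and y = a + b(x + e) be ex vivo depth, with b > 0 and e the measurement error. Then corr(x, y) = corr(x, x + e), so a (constant shift) and b (proportional change) both drop out. The sentence on depth of invasion does not name the coefficient. The paragraph uses Pearson's; a rank coefficient would be equally blind to a and b.

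**3. Numerical illustration.** The documents give no distribution of depth or of paired differences, so these inputs are assumptions: mean 8 mm, SD 4 mm, error SD 1.5 mm, one simulated set of n = 27.

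| Change from in vivo to ex vivo | r | Mean difference (mm) | 95% limits of agreement (mm) | Paired t-test p |
|---|---|---|---|---|
| None | 0.933 | 0.0 | −2.59 to 2.58 | 0.99 |
| 2 mm lower | 0.933 | −2.0 | −4.59 to 0.58 | 2 × 10⁻⁸ |
| 4 mm lower | 0.933 | −4.0 | −6.59 to −1.42 | 8 × 10⁻¹⁵ |
| 20% smaller | 0.933 | −1.5 | −4.14 to 1.05 | 2 × 10⁻⁶ |

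The coefficient is the same in all four rows; the paired difference separates them.

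**4. How large might a shift be?** The documents do not say. As an illustration only, uniform shrinkage of 10% to 30% would move a 10 mm depth by 10 × 0.10 = 1 mm to 10 × 0.30 = 3 mm, and a 5 mm depth by 0.5 to 1.5 mm.

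**5. Is the planned sample useful for a paired difference?** Section 6 states no figure for depth of invasion. Its calculation "is calculated to achieve a significance level of 0.05 and 90% power" and concerns free-margin frequency, 55% against 16%. The stated 27 is reproduced by the unpooled two-proportion formula with two-sided α:

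(1.960 + 1.282)² × (0.55 × 0.45 + 0.16 × 0.84) / 0.39² = 26.4, rounded up to 27; and 27 / 0.90 = 30.

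With 27 pairs, the 95% CI half-width for the mean difference is t(0.975, 26) × SD / √27. The SD of paired differences is assumed over a range:

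| SD of differences (mm) | CI half-width (mm) | Power, 1 mm shift | Power, 2 mm shift |
|---|---|---|---|
| 1 | 0.40 | 99.9% | over 99% |
| 1.5 | 0.59 | 92% | over 99% |
| 2 | 0.79 | 71% | over 99% |
| 3 | 1.19 | 39% | 92% |

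The shift detectable with 80% or 90% power is 0.56 or 0.65 SD. The sample planned for another purpose would therefore give an informative estimate here, except for small shifts with noisy differences.

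**6. Where does histology enter?** The first depth-of-invasion item in Section 4 sets 3D ultrasound and MRI depth against histology slides. No sentence sets in vivo depth against histology. The ex vivo versus histology comparison cannot fill the gap, because both of its measurements are taken after resection.

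**The case against.** The strongest reply is that this is a condensed article. Section 5 says the correlation will be reported in addition; it does not say that nothing else will be. The authors plan paired tests and Bland–Altman plots in the same paragraph, and an analysis plan that is not shown could extend them to this pair. That possibility stands. But the article does more than stay silent: it names a method for a primary item, and it words the agreement methods so that this pair falls outside them.

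The stakes are also limited. The research question concerns margins and the sample size concerns free-margin status; this pair feeds neither.

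Some stronger readings are tempting, and the documents do not support them:

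- A reader might infer that depth of invasion is never set against histology, or that the study cannot judge the accuracy of either scan. Section 4 does plan a histology comparison for ex vivo 3D ultrasound and MRI depth. Only in vivo depth lacks one.
- A reader might see a conflict with the opening sentence of Section 4, which sets index tests against histopathology. That sentence is about margin assessment, so comparing two ultrasound settings does not contradict it.
- A reader might take near-perfect correlation alongside a shift of several millimetres as the expected result. The shrinkage range is an assumption, and r equals 1 only with uniform shrinkage and no measurement error.
- A reader might conclude that the item should become secondary. Nothing in the argument requires that.

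Finally, it is not certain that histological depth is measured as a routine item. Section 3.2.4 lists margin status, tumour delineation, tumour volume and five smallest margins; depth of invasion on slides is implied only by the Section 4 item.

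**Conclusion.** The point holds in a limited form. For one item of the primary outcome, the stated analysis cannot reveal the systematic change that an in vivo versus ex vivo comparison would be expected to show, and no other method in Section 5 covers that pair. This follows from the wording and from the algebra of correlation; it does not rest on any assumed shrinkage. How large an undetected shift might be cannot be derived from the documents, and the millimetre figures above are illustrations under stated assumptions. The absence of an in vivo versus histology comparison is a smaller, related gap. The margin results and the sample size are unaffected. The correction is worth making because it is easy and the item is labelled primary.

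**What to change.** In Section 5, for in vivo versus ex vivo ultrasound depth of invasion, state that the paired mean difference with its 95% CI and the Bland–Altman limits of agreement will be reported, with a check for proportional bias (for example, regression of the difference on the mean of the two readings). Keep the correlation as a descriptive figure. Where histological depth is recorded for the image-by-image outcome, report the same agreement analysis for in vivo depth against histology.

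Both ultrasound measurements are already planned, so the first change costs a sentence and a little extra analysis. The histology part is equally light where histological depth is recorded; the protocol should confirm that it is. The outcome's rank need not change.

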#### 3.2.4. Tissue Preparation and Histopathology

After conducting the MRI scan in the radiology department, the surgical specimen will be returned to the pathology department for formalin fixation. 

In the pathology department, the samples will be treated using standard procedures to create formalin-fixed, paraffin-embedded (FFPE) blocks of tissue. The samples are first formalin-fixed with 10% formaldehyde for 24 h. Before starting the slicing procedure of the specimen by the pathologist, the formalin-fixated specimen will again undergo 3D ultrasound. Then a pathologist will perform parallel slicing, with almost equal intervals (~2 mm). The slices are then transferred to cassettes for further processing and embedded in paraffin to form FFPE blocks, which are cut at 4 μm and mounted on glass slides. Afterwards, the slides will be stained with hematoxylin and eosin (H&E) to visualize the tissue under the microscope. Two pathologists will assess the surgical margin status and will delineate the tumor on the slides. The tumor volume in milliliters (mL) will be estimated by the multiplication of the tumor area per slice and the cutting intervals. The pathologist will also measure the smallest margin at the posterior, anterior, lateral, medial, and profound directions (as described in Figure 1). The average measurement obtained by the two pathologists will be considered as the gold standard.

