The intra- and interobserver variability will be quantified by calculating the intraclass correlation coefficient (ICC). The ICC measures the reliability of the measurements between the two observers and is the measure of the degree of agreement among the observers in their assessment of margin status.

We will also classify the data into three categories of positive (<1 mm), close (between 1–5 mm), and free (>5 mm) margins. For each included case, we will compare the accuracy of each index test by computing the proportion of correctly classified margins with respect to the reference standard class. We will use the McNemar test to determine if the proportions of categories in the index tests differ significantly from those of the reference standard (paired categorical data). The results will be considered statistically significant when *p* < 0.05, with a 95% confidence interval. 

The mean time spent on delineation by the operators will be recorded and reported in minutes. Data will be analyzed with commercially available software (RStudio Team-2023). RStudio: Integrated Development for R. RStudio, Inc., Boston, MA, USA.

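### The protocol calls the ICC on millimetre readings the measure of reader agreement on margin status, but that ICC does not determine agreement on the positive/close/free class

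*Protocol article*

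**What the plan says.** Section 5 (Statistics) quantifies variability within and between observers by the ICC and names no other reader-agreement statistic. It gives the ICC two meanings in one sentence. The first is "The ICC measures the reliability of the measurements between the two observers"; earlier in the same section margin measurements are defined as quantitative values in mm. The second is that the ICC "is the measure of the degree of agreement among the observers in their assessment of margin status".

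The next paragraph brings in the classes: "We will also classify the data into three categories of positive (<1 mm), close (between 1–5 mm), and free (>5 mm) margins". There they serve only to compare each index test with histopathology, by proportion correct and the McNemar test. Section 4 lists among the primary outcomes "The number of margins correctly classified as free (>5 mm), close (1–5 mm), or positive (<1 mm) margins by 3D ultrasound and MRI", with histopathology as the reference.

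Elsewhere the word status denotes the class. Section 3.2.4 says "Two pathologists will assess the surgical margin status and will delineate the tumor on the slides" and lists the measurement of the smallest margin in each direction as a separate task. Section 6 gives free margin status as a frequency (55% and 16%).

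**The concern.** An ICC on millimetre readings is the share of total variance that comes from true differences between margins. It does not use the 1 mm and 5 mm limits. Two readers can differ by a fraction of a millimetre, which barely moves the ICC, and still put a margin in different classes. They can also differ by more than that on wide margins and always agree that the margin is free.

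At stake is what can be said about the reproducibility of margin status for the ultrasound readers, the radiologists, and the two pathologists who form the reference. As section 5 is worded, a high ICC could be presented as agreement on status although class agreement was never examined. The Introduction links positive and close margins to recurrence and adjuvant treatment, so agreement at the cut-offs is the clinically relevant kind.

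**Working it through.** The protocol states no ICC value, target or precision, so there is no figure of its own to reproduce. The check is an illustration.

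**Inputs from the documents**
- Classes: positive <1 mm, close 1–5 mm, free >5 mm (sections 4 and 5).
- Class mix: 10% positive and 74% close (Introduction, retrospective series of 91 resections), which leaves 100 − 10 − 74 = 16% free.

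**Assumptions**
- True margins are normally distributed.
- The per-case mix stands in for the mix of single margins.
- Each reader gives one unbiased reading, with independent normal errors of equal SD.

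**Step 1: fit the distribution.** P(<1 mm) = 0.10 and P(>5 mm) = 0.16 give normal quantiles of −1.282 and 0.994.
- SD = (5 − 1)/(0.994 + 1.282) = 1.757 mm
- Mean = 1 + 1.282 × 1.757 = 3.252 mm

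**Step 2: reader error for a given ICC.** ICC = SD²/(SD² + error²), so error = SD × √(1/ICC − 1).
- ICC 0.90: 1.757 × √0.1111 = 0.59 mm
- ICC 0.80: 1.757 × √0.25 = 0.88 mm

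**Step 3: class agreement between two readers** (simulation, 2,000,000 margins)

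| ICC (mm) | Class differs | Unweighted kappa | Quadratic-weighted kappa | Agreement specific to positive |
|---|---|---|---|---|
| 0.90 | 16% | 0.64 | 0.72 | 0.70 |
| 0.80 | 24% | 0.50 | 0.61 | 0.59 |

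**Step 4: averaged readings.** Section 5 presents margins as the average of two repetitions. If the error is divided by √2, two independent averages at a single-reading ICC of 0.90 differ on class for 11% of margins (unweighted kappa 0.74, quadratic-weighted 0.79).

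**Step 5: other assumed distributions.** At an ICC of about 0.90 (simulation, 400,000 margins each, readings floored at 0 mm):

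| True margins | Class agreement | Unweighted kappa |
|---|---|---|
| Lognormal, same 10/74/16 mix | 75% | 0.49 |
| Normal, same mix | 84% | 0.64 |
| Wide spread, median 6 mm | 70% | 0.41 |
| Narrow spread, mean 5 mm, SD 1.5 mm | 85% | 0.71 |

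**Step 6: the ICC does not fix class agreement in either direction.**
- High ICC, poor class agreement: ten constructed margins, several at the cut-offs, with reader differences of at most 0.5 mm, give ICC 0.997, class agreement 40% and kappa −0.03.
- Low ICC, near-perfect class agreement: margins around 10 mm (SD 1 mm, reader error SD 1 mm) give ICC 0.50 and class agreement 99.96%.

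**Step 7: effect of spread at fixed reader error.** With mean 3.25 mm and error SD 1.0 mm, the true SD is widened from 1.76 to 4 mm:
- ICC rises from 0.76 to 0.94.
- Class disagreement falls from 27% to 19%.
- Unweighted kappa rises from 0.44 to 0.71, and quadratic-weighted kappa from about 0.58 to 0.84.

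Kappa therefore depends on the spread of margins too. The error SD in mm does not.

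**The case against.** The fault can be called half a sentence. An ICC suits the millimetre readings, and margin status may be no more than a loose gloss. If the ICC were instead computed on ordinal class codes, it would be practically the quadratic-weighted kappa (the two coincide in the simulation). That reading is hard to sustain, because section 5 ties the ICC to the measurements and brings in the classes only in the following paragraph.

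It can also be said that reader agreement is neither a primary nor a secondary outcome, and that the form of the ICC, the kappa weights and the interval method belong in an analysis plan that is not shown. This stands for the missing detail. It does not cover the statement itself: the article names the statistic and says what it shows, and for status that is not right.

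Three stronger readings go beyond the documents:
- A reader might infer that a high ICC would conceal disagreement that is actually present. The documents hold no reader data, and the 10 mm example shows that class agreement can be near perfect. The claim is only that the ICC cannot tell.
- A reader might infer that kappa is better because the ICC rises with the spread of margins. Kappa rises as well (step 7), so spread is no argument for it. The argument is that kappa and raw agreement use the cut-offs.
- A reader might take 16% as the expected disagreement in this trial. It rests on per-case percentages applied to single margins and on single readings, whereas the plan averages two readings.

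**Conclusion.** The point holds as a minor improvement. Section 5 assigns to a millimetre ICC a meaning, agreement on margin status, that it does not have, and names no statistic that does have it. Under the assumptions above, an ICC of 0.90 goes with different classes on about 16% of margins for single readings and about 11% for averages of two. Over the four assumed distributions the single-reading figure runs from 15% to 30%. These are illustrations, not predictions. The planned comparison of each index test with histopathology does not use the ICC and is unaffected. What changes is what may be concluded about the reproducibility of the classes behind a primary outcome.

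**What to change.** In section 5:
1. Limit the ICC to the millimetre readings and remove the statement that it measures agreement on margin status. Report the within-reader and between-reader error SD in mm beside it.
2. For margin status, report weighted kappa on the three classes together with percent agreement and class-specific agreement, above all for positive margins.
3. Compute these from the individual readings, before averaging, for each reader pair: the two surgeons reading ultrasound, the two radiologists and the two pathologists.
4. Use intervals that allow for five margins per patient, for example by resampling patients.

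The cost is analysis work only. The two-reader design in sections 3.2.2 to 3.2.4 already yields the readings, so no further scan, reader or patient is needed. The drawback is that kappa will be imprecise with 27 to 30 patients and, like the ICC, depends on the mix of margins, so it should be read alongside the raw agreement.

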## 1. Introduction

Oral squamous cell carcinoma (SCC) is the eighth most common cancer worldwide, with less than 60% of the patients surviving more than 5 years [1]. In a study conducted at our center (Department of Otorhinolaryngology, Head and Neck Surgery, and Audiology, Rigshospitalet, University of Copenhagen, Copenhagen, Denmark), among 8299 oral cancer patients, it was found that the 5-year overall survival rate was 43% for women and 36% for men [2]. SCC of the tongue is the most common type of oral cavity cancer, and the primary treatment for patients with early stages of tongue SCC is surgery [3,4]. The main goal of surgical oncology is to entirely remove the tumor, along with a margin of healthy tissue surrounding it, to ensure proper cancer removal. At the same time, preserving as much healthy tissue as possible during tongue cancer surgery ensures the quality of life for the patient, maintaining vital functions such as swallowing and speaking after surgical treatment. Survival and the need for postoperative treatment are highly dependent on the accuracy of the surgical resection margins for the cancer. Inadequate surgical margins (margin ≤ 5 mm) may lead to a second resection [5]. The presence of positive (<1 mm) or close (1–5 mm) margins following cancer surgery leads to an increased risk of local cancer recurrence, reduces the chance of survival, and necessitates adjuvant treatments, such as radiotherapy or chemoradiation. In a study at our center investigating 1399 patients with oral squamous cell carcinoma (OSCC), 44% of the cases received adjuvant radiotherapy after surgery [6]. A recent retrospective analysis of 91 tongue SCC resections reported a total of 74% of the cases with close margins (1–5 mm) and 10% with positive margins (<1 mm) [7]. Given the significant impact of surgical precision on patient outcomes in oral squamous cell carcinoma (SCC), there is a pressing need for advanced intraoperative techniques to ensure complete tumor resection. The potential for positive surgical margins, which can lead to the necessity for additional treatments or even further surgery, underscores the critical need for more accurate and efficient intraoperative techniques. Therefore, the development and implementation of innovative approaches that can improve the rate of complete tumor resection are not only desirable but essential for enhancing surgical care and ultimately improving patient survival rates and quality of life [8].

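### The classification comparison rests on the raw proportion of margins in the correct class, which can rank a test that misses inadequate margins above one that finds them

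*Protocol article*

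**What the plan says.** Section 5 (Statistics) sorts margins into positive (<1 mm), close (1–5 mm) and free (>5 mm), and compares the accuracy of each index test by "computing the proportion of correctly classified margins with respect to the reference standard class". Section 4 (Clinical Outcome Definition) puts this under the primary outcome: "The number of margins correctly classified as free (>5 mm), close (1–5 mm), or positive (<1 mm) margins by 3D ultrasound and MRI", with histopathology as reference. The unit is the single margin: "Each case will undergo five margin measurements".

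One significance test is attached to the classes: "We will use the McNemar test to determine if the proportions of categories in the index tests differ significantly from those of the reference standard". For the millimetre values, Section 5 plans paired t-tests, Pearson correlation and Bland–Altman plots. The intraclass correlation is for observer variability.

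Section 1 (Introduction) sets out the clinical decision. A margin of 5 mm or less is inadequate and may lead to a second resection, and positive or close margins lead to adjuvant treatment. The only full class mix in the article is in the same section and comes from an outside series: "A recent retrospective analysis of 91 tongue SCC resections reported a total of 74% of the cases with close margins", and 10% with positive margins.

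**The concern.** Section 8 (Discussion) states the aim as showing whether 3D ultrasound has a higher diagnostic rate than MRI and the surgeon's examination. For the margin classes, the number that would show this is the overall proportion correct. That number is a weighted average of the class-specific correct rates, and the weights are the class shares, so the commonest class dominates it.

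The classes are also ordered, and the errors are not equal. A positive margin called free would leave tumour at the edge unrecognised. In the planned measure it costs exactly as much as a close margin called free, or a free margin called close.

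At stake is the ranking of the three modalities on a primary item. A modality that leans towards the commonest class could come out ahead although it misses more of the margins that the technique is meant to detect.

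**Working it through.** **The plan's own figures.** The protocol states no expected classification accuracy, so there is none to reproduce. Its 27 analysable cases (30 after 10% drop-out: 27/0.9 = 30) come from free-margin frequencies of 55% and 16%. They are used below only to count margins, and this point does not affect them.

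**Formula.** Proportion correct = Σ (class share × correct rate in that class).

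**Comparison test (assumed).** Correct in 80% of positive, 70% of close and 80% of free margins, called 80/70/80 below.

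**Case level.** Section 1 gives 10% positive and 74% close, which leaves 100 − 74 − 10 = 16% free.

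- *Always close*: 0.10×0 + 0.74×1 + 0.16×0 = 74.0%.
- 80/70/80 test: 0.10×0.80 + 0.74×0.70 + 0.16×0.80 = 0.080 + 0.518 + 0.128 = 72.6%.

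The uninformative test ranks first. The mean of the three class-specific rates reverses the order: 33.3% against (80 + 70 + 80)/3 = 76.7%.

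**Margin level, the unit analysed.** The article gives no margin-level mix, so one must be assumed. Suppose that each case that is not free has exactly one inadequate margin, and that its other four are free.

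- Positive: 0.10/5 = 2.0%. Close: 0.74/5 = 14.8%. Free: (0.16×5 + 0.84×4)/5 = 83.2%.
- *Always free*: 83.2%.
- 80/70/80 test: 0.020×0.80 + 0.148×0.70 + 0.832×0.80 = 0.016 + 0.1036 + 0.6656 = 78.5%.

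For detecting a margin of 5 mm or less, *always free* has sensitivity 0%. The 80/70/80 test has at least (0.016 + 0.1036)/0.168 = 71%, even if every one of its errors on inadequate margins is a call of free.

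**How far this depends on the mix.** Let q be the share of the other four margins that are free in cases that are not free, with the rest close. The free share is 0.16 + 0.84×0.8×q.

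| q | Positive / close / free (%) | *Always close* | *Always free* | 80/70/80 test |
|---|---|---|---|---|
| 1.0 | 2.0 / 14.8 / 83.2 | 14.8% | 83.2% | 78.5% |
| 0.9 | 2.0 / 21.5 / 76.5 | 21.5% | 76.5% | 77.8% |
| 0.7 | 2.0 / 35.0 / 63.0 | 35.0% | 63.0% | 76.5% |
| 0.5 | 2.0 / 48.4 / 49.6 | 48.4% | 49.6% | 75.2% |
| 0.3 | 2.0 / 61.8 / 36.2 | 61.8% | 36.2% | 73.8% |
| 0 | 2.0 / 82.0 / 16.0 | 82.0% | 16.0% | 71.8% |

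A constant call beats this particular test at the two ends and not between them. A weaker but still informative test is overtaken in less extreme mixes. Take five independent, identically distributed margins whose worst one gives 10/74/16. The free share is 0.16^(1/5) = 69.3%, the positive share is 1 − 0.90^(1/5) = 2.1%, and the close share is 28.6%. *Always free* scores 69.3%. A test correct in 80%, 60% and 65% scores 0.021×0.80 + 0.286×0.60 + 0.693×0.65 = 63.9%. In this mix the 80/70/80 test scores 77.1% and is ranked correctly.

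**The McNemar test as a guard.** With 27 cases at the case-level mix, *always close* disagrees with the reference in 0.26×27 ≈ 7 cases, all in one direction. The exact two-sided p is 2×0.5^7 = 0.016, so a constant test would probably be flagged. The test sees only marginal shares, however. A modality with the right share in each class but the wrong margins in each passes it.

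**The case against.** The strongest objection concerns the 74%. A reader might infer that the trial expects 74% of its margins to be close, so that always saying close would score 74% on this outcome. The documents do not support that. The figure is a share of resections in an outside retrospective series, whereas the outcome counts five margins per case. At margin level *always close* could score anywhere from about 15% to 82%, and *always free* may well be the better constant call. This objection stands, and the 74.0% is used here only as a case-level illustration.

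Second, a reader might infer that raw accuracy is the plan's only measure of accuracy. It is not. The millimetre differences are listed first among the primary outcomes, and those analyses reflect the size of each error and would expose a constant test. The McNemar test would often flag one too. These are real guards, but partial ones. None reports how often a margin of 5 mm or less is missed, and the McNemar test does not compare the index tests with each other.

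Third, real modalities return millimetre values, so a constant call is artificial, and the 80/70/80 test is assumed. That is fair. The constant call is the limiting case of a test that leans towards the commonest class.

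Fourth, Section 4 could be read as asking for counts by class, which would give class-specific rates, and an article may leave tables to a fuller document. The wording in Section 4 does allow that. Section 5, however, names the measure on which the index tests are compared, and that is the overall proportion. The point is about this stated choice, not about missing detail.

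**Conclusion.** The point holds as a weakness in a stated analysis. The proportion correct depends on the class mix, rewards the commonest class and ignores the order of the classes, so it is a poor basis for ranking the modalities on a primary item. It can place a test that finds no inadequate margin above one that finds at least 71% of them (83.2% against 78.5%). That result assumes one inadequate margin per case that is not free, and the 80/70/80 test.

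The documents do not show that a wrong ranking will occur. Under several plausible margin mixes the 80/70/80 test is ranked correctly, and the true mix is unknown. The data and the sample size figure are not affected. The plan should be changed on this point, but the trial is not invalid because of it.

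**What to change.** In Sections 4 and 5, for each index test against histopathology:

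- Make sensitivity and specificity for an inadequate margin (≤5 mm against >5 mm) the main classification measure.
- Add as supporting measures the full 3×3 table, weighted kappa, and sensitivity and specificity for a positive margin (<1 mm).
- Give 95% confidence intervals that account for five margins per patient, for example by resampling patients.
- Keep the proportion correct as a descriptive figure.

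This changes analysis wording only and uses the same data. The cost is visible imprecision. With 27 cases there are 27×5 = 135 margins. Under the one-inadequate-margin assumption about 0.168×135 ≈ 23 are inadequate, so a sensitivity of 80% has an approximate half-width of 1.96×√(0.8×0.2/23) = 16 percentage points. About 0.02×135 ≈ 3 margins are positive. Even if all 3 are detected, the exact 95% interval runs from 0.025^(1/3) = 29% to 100%, which is why sensitivity for positive margins should be supporting and not the main measure.
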